The units were sorted from one to 12 according to the number of geriatric beds and then stratified into three strata: four clusters with 16 to 23 beds, six clusters with 6 to 10 beds and two clusters with 4 and 5 beds respectively. In each block, the clusters were randomized to either the intervention or the control arm with an allocation ratio of 1:1. An independent professor in epidemiology performed the allocation using the Microsoft Excel RAND-function, only knowing the numbers of the clusters. The randomization was performed to achieve a balance in unit types in the intervention and control arm and a similar size of the two arms including a similar number of admitted patients filling the inclusion criteria. All hospitals are located in cities or towns. The purpose of the stratification was primarily to achieve a balance in the number of patients and next of kin between the two arms, and secondly to include units of various sizes in both.

The study has primary outcomes for the implementation and for the clinical effectiveness. The primary outcome for the implementation outcome sub-study is the differences in fidelity changes between the arms. The unit of analysis for the fidelity scores is the health care units or clusters. Fidelity is rated on 5-point scales (1 = poor fidelity, 5 = high fidelity). Based on previous research (mean difference 1.82 and average SD 0.80 after 18 months with implementation support), we have calculated that we need at least four clusters in each arm to show that implementation support gives a significant increase in fidelity, based on 5% two-tailed significance and 80% power. If the differences are smaller in our study, we will need a larger sample. Due to the possibility of unit drop-out during the project period and to secure sufficient power, we have included six units in the intervention arm and six in the control arm.

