#### Patient outcomes

##### Questionnaire

Patients in the triadic sub-study will be asked to answer a short questionnaire including the following dimensions:Quality of communication and decision-making for the patient and the next-of-kin when approaching the end of life (primary outcome for patients)Communication about preferences for information and involvement, health care personnel’ current compliance with these preferences, and trust in future complianceSatisfaction with information about the patient’s state of health, discharge, prognosis, and future health care needs, and with information and involvement concerning health care provided during and after admittanceSelf-efficacy in communicating with next-of-kin and health care professionals about future deterioration, about preferences for life-prolonging treatment in such a situation, and about health care when approaching the end of lifeProblem causing admittance being solved; satisfaction with arrival, stay, and discharge at the hospital; and trust in necessary health care in the futureConcrete preferences for information and who should participate in important decisions about health care, and assessment of the amount of information givenGeneral life satisfaction [48]Demographic information

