#### Attending clinician outcomes

##### Questionnaire

Attending clinicians in the triadic sub-study will be asked to answer a questionnaire including the following dimensions:Clinical information about the patientThe professional role towards the patientThe patient’s concrete preferences for information and who should participate in important decisions about health care, and assessment of the amount of information given (primary outcome for attending clinicians is the congruence between the clinician’s answer and the patient’s answer on these questions)Self-confidence in matching involvement of patient and next-of-kin and future decision-making to patient’s preferencesSelf-efficacy in communicating about: future deterioration, preferences for life-prolonging treatment in such a situation, future care (at home or in a nursing home), and about health care when approaching the end of life, with the patient, next-of-kin, and other health care personnelDemographic information

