### Health economics

The economics analysis includes estimation of healthcare utilization, costs and cost-effectiveness of ACP and the implementation support in geriatric hospital units compared to standard of care. We will identify the resource use and costs related to implementing and conducting ACP in clinical practice, and we will estimate patient’s healthcare utilization and costs in order to identify differences in pathways as a result of implementation of ACP. Higher costs after implementation may indicate underutilization and lower costs may indicate overutilization of healthcare without ACP. The information on healthcare utilization will be collected from national registries covering both pharmaceuticals and primary, secondary, home based and institutional based care.

Resource use and healthcare utilization will be summarized over 18 months prior to inclusion in the trial and 18 months after. Total costs will be calculated, and we will use regression analysis to estimate the effect of ACP on total costs, also adjusting for individual characteristics, such as age, gender, comorbidity, living situation, social network, marital status and education measured at inclusion. We will also estimate the cost-effectiveness of implementation of ACP compared to standard of care. The costs will include intervention costs of ACP and the cost of the hospital stay. Differences in costs will be compared to the primary outcomes (measured as percentage point difference in quality of communication and decision-making for patients and for next of kin, congruence (attending clinicians) and fidelity (implementation outcome) and selected secondary outcomes. We will use the incremental cost-effectiveness ratio, defined as differences in costs between implementation of ACP compared to standard of care divided by percentage difference in primary (selected secondary) outcomes (ACP and standard of care). Uncertainty will be estimated by bootstrap methods and displayed in a cost-effectiveness plane.

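### The cost-effectiveness ratio is given an absolute effect measure in one sentence and a relative one in the next; for 1-5 fidelity scores the two differ by a factor of about 1.3 to 2.7

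*Protocol article*

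**What the plan says.** The Health economics section plans a cost-effectiveness analysis in which cost differences are set against the primary outcomes and selected secondary outcomes. The primary outcomes are to be "measured as percentage point difference in quality of communication and decision-making for patients and for next of kin", and the same parenthesis goes on to list clinician congruence and fidelity. The following sentence defines the incremental cost-effectiveness ratio as the cost difference between arms "divided by percentage difference in primary (selected secondary) outcomes".

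The scale of the outcomes is documented unevenly. In the section on cluster selection and sample size: "Fidelity is rated on 5-point scales (1 = poor fidelity, 5 = high fidelity". The section on the fidelity outcome repeats the 1 to 5 item scoring. The patient outcome is named only as a questionnaire dimension, without a score range, and the same holds for next of kin. For clinicians, the "primary outcome for attending clinicians is the congruence between the clinician’s answer and the patient’s answer on these questions", again without a stated scale. The triadic data analysis section compares mean outcomes with linear mixed models.

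A separate regression is planned for total costs, "also adjusting for individual characteristics, such as age, gender, comorbidity, living situation, social network, marital status and education". Resource use is summarised for 18 months before and 18 months after inclusion.

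**The concern.** A percentage point difference subtracts one percentage from another. A percentage difference divides by a reference value. Using both for the denominator of one ratio leaves the ratio undefined, and an analyst could follow either sentence and be in line with the plan.

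For fidelity the trouble goes past the choice of word. A mean of 1-5 scores is not a percentage, so percentage points exist only after a rescaling, which is not given. A relative percentage can be computed, but it depends on where the scale happens to start and on the control value, neither of which says anything about the size of the benefit. At stake is the published cost per unit of effect, which is part of a listed secondary objective. The primary tests are not touched.

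A smaller, separate matter is the total-cost regression. The article does not say whether total costs means the post-inclusion sum, both periods together, or a change, and it does not name prior cost as a covariate although it is collected.

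**Working it through.** The article states no figure for the ratio, so there is none to reproduce. The check compares the two definitions on fidelity.

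**Inputs.** Scale 1 to 5 and planning difference d = 1.82 points: from the section on cluster selection and sample size. Control mean C: not in the article; assumed 1.5, 2.0, 2.5 and 3.0. With d = 1.82 and a ceiling of 5, C cannot exceed 5 − 1.82 = 3.18.

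**Absolute reading.** Rescaling by (x − 1)/4 gives 100 × 1.82/4 = 45.5 percentage points. Rescaling by x/5 gives 100 × 1.82/5 = 36.4. The unstated rescaling alone therefore moves the result by 45.5/36.4 = 1.25.

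**Relative reading.** 100 × d/C. Divided by the absolute reading with (x − 1)/4, this is (d/C)/(d/4) = 4/C, whatever the value of d.

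| Assumed control mean | Percentage points, (x − 1)/4 | Relative % | Ratio, 4/C |
|---|---|---|---|
| 1.5 | 45.5 | 121.3 | 2.67 |
| 2.0 | 45.5 | 91.0 | 2.00 |
| 2.5 | 45.5 | 72.8 | 1.60 |
| 3.0 | 45.5 | 60.7 | 1.33 |

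At a fixed cost difference, the cost per 1% is smaller than the cost per percentage point by the factor in the last column.

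**Dependence on the starting value.** At C = 2.0 the relative gain is 1.82/2.0 = 91%. If the same scores are shifted to start at zero, it is 1.82/1.0 = 182%. The difference in points is 1.82 both times. The article does not use a scale starting at zero; the shift only shows that the relative figure is a product of the coding.

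**Reference value.** The primary fidelity outcome is the between-arm difference in change from baseline. If the percentage were taken relative to the control arm's change, the reference could be close to zero, since the Discussion considers it unlikely that control units will implement advance care planning. The relative measure would then be unstable. The article does not say which reference is meant.

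**Prior cost as a covariate.** If r is the correlation between pre- and post-inclusion cost (assumed, not in the article), person-level variance is multiplied by 1 − r². For r = 0.3 this is 1 − 0.09 = 0.91; for r = 0.5 it is 1 − 0.25 = 0.75. So 9% to 25% is removed, and the standard error is multiplied by 0.95 to 0.87. These are upper limits at those correlations: comorbidity, age and the other covariates will already explain part of the same variance, and the between-unit variance is ignored.

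**The case against.** The strongest reply is that this is a slip of one word. The authors may mean percentage points in both sentences, and a condensed article may leave scoring and rescaling to the analysis plan. That is plausible, and missing instrument detail alone would be no finding. But the article does not leave the definition open. It gives it twice, in adjacent sentences, with different meanings.

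The practical effect is also limited. If the reference is a positive control mean score, moving from absolute to relative units cannot change the sign of the effect. Bootstrap points stay in the same quadrant of the cost-effectiveness plane, and the article names no threshold that a change of units could cross. This stands, though it would not cover a relative measure based on the control arm's change.

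Several stronger readings might be inferred, and the article does not support them:

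- *All primary outcomes are 1-5 scores.* This range is documented for fidelity only. If congruence is analysed as a proportion, a percentage point difference is well defined for it.
- *The ratio could differ four-fold.* That needs 0-4 scoring, which the article never uses. Even a factor of two needs a control mean of about 2 or below.
- *The cost regression wrongly leaves out prior cost.* The covariate list is introduced as examples and is open, so prior cost is unnamed, not excluded. Nor would adjusting for it necessarily alter the ratio: that regression is described separately, and the ratio's costs are said to include the intervention and the hospital stay.
- *Clustering is mishandled in the cost model or the bootstrap.* The article does not specify either in enough detail to be wrong.

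**Conclusion.** The inconsistency is real and should be corrected before costs and effects are analysed. One ratio has two non-equivalent denominators. For fidelity neither reading can be applied unambiguously: the absolute one lacks its rescaling, and the relative one depends on the coding and the reference value. The readings differ by a factor of 1.33 to 2.67, assuming control means of 3.0 to 1.5 and rescaling by (x − 1)/4. For the patient, next-of-kin and clinician outcomes the contradiction in wording is the same, but its size cannot be computed because their scales are not given. What changes is the size and meaning of the reported ratio, not the direction of a conclusion, provided the reference is a positive mean score.

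The prior-cost point is an opportunity to gain precision and some protection against baseline imbalance with only 12 units. It is not an error in the plan.

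**What to change.** Use one absolute denominator throughout the Health economics section and delete the reference to a percentage difference. For outcomes analysed as means, use the between-arm difference in score points, or a 0-100 rescaling with its formula stated, for example 100 × (x − 1)/4 for fidelity. For any outcome analysed as a proportion, use the risk difference in percentage points. Take each effect estimate from the corresponding effectiveness analysis, so that the denominator is the effect reported there.

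As an optional addition, state that total costs means costs after inclusion, and name the 18-month pre-inclusion cost as a covariate in the total-cost regression.

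The cost is a few words in the analysis plan and one more regression coefficient. No new data are needed. The one drawback is that ratios in raw score points cannot be read side by side across outcomes with different ranges; the 0-100 rescaling puts them on a common range if that is wanted.

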### Reporting

The project will be evaluated comprehensively, and the sub-studies described below will be published in international scientific journals. We will also work to incorporate important knowledge and experience with ACP gained through the project to the curriculums for health care personnel and relevant national guidelines.

### Data management and monitoring

The University of Oslo has signed contracts on shared responsibility for data processing with each participating Health Trust, which details the responsibilities for data collection and storage in accordance with Norwegian legislation and the General Data Protection Regulation. Since the Norwegian ACP trial is a minimal risk trial, we do not have a data monitoring committee. Project members will monitor the recruitment process and participate and monitor the data collection and have signed a similar contract to ensure conformity with the trial’s ethical and methodological standards. Data will be stored in a secure database, developed by the University of Oslo to collect, store and analyze sensitive research data in a secure environment “Services for sensitive data” (TSD). Only project members (researchers and scientific assistants) have access to the secure project area.

For the digital questionnaires, the respondents will fill out the questionnaire in the electronic “nettskjema”-application by UiO, which encrypts and stores the answers directly in TSD. Patients will in addition have the option to fill in questionnaires on paper. The participating institutions will collect consent and data from patients and next of kin in their respective institutions and be responsible for data management until delivered personally to a member of the project group for import to TSD. Paper questionnaires and consent forms will be stored in locked cupboards, whereas code lists with personal information will be safely stored digitally in secure databases in the Hospital Trusts. All participating institutions have appointed a research coordinator responsible for data collection and safe storage at each site.

Individual interviews and focus groups will be audio recorded with digital recorders and transferred to TSD via UiO-computers the same day; or with a secure voice recorder app developed for phones by UiO, which encrypts and transfers the interview directly in TSD.

### Research ethics

The study was approved by Norwegian Agency for Shared Services in Education and Research (SIKT) with registration number 805491 and by local data protection officers at each trial site. Important protocol modifications will be reported to SIKT and communicated to the participating units, and the trial registry at clinicaltrials.gov will also be updated. The project will follow the Norwegian personal data legislation and regulation, the Norwegian Health Research Act, the guiding principle of the Declaration of Helsinki [65], as well as ethical standards as described by The National Committee for Medical and Health Research Ethics (NEM) and Committees for Medical Research Ethics (REK), e.g., about informed consent, privacy, and subject withdrawal.

Hospitalized patients and their next-of-kin can be considered a particularly vulnerable group. Special attention will be paid to assessment of capacity to consent and will only include participants with capacity to decide to participate in research. Thorough oral and written information will be provided, and written consent will be obtained from all participants. The participants can withdraw from the study at any time without giving any reason. Neither participation nor non-participation in the research will have any consequences for patient treatment, including to be invited to ACP.

## Discussion

This project is a contribution to a shift in the health services towards including a holistic patient perspective and to ensure patient-centered care in the management and treatment of older adults approaching the end-of-life. This will be the first trial to develop and test an intervention to improve the implementation of ACP for acutely ill and frail older adults in geriatric hospital wards in Norway. This complex multicenter project is both an implementation and an intervention study, which requires a mixed methods approach and measurement of outcomes on multiple levels [26, 27]. The pragmatic cluster randomized design allows comparing outcomes between intervention and control arm on implementation- and service level, by measuring fidelity scores, as well as patient and relative level, by questionnaires, patient record data and health registers.

The ACP interventions in the intervention arm will be compared to treatment as usual in the control arm. Although the control clusters in theory may implement ACP during the project period, we consider this unlikely, due to the lack of incentives and the complexity of the intervention. What we do know, however, is that elements of ACP are used in communication with patients and their relatives in geriatric units already, although not systematically. Improving routines and quality of existing communication may not result in large differences in outcomes for patient- and next of kin in the intervention- and control arms. To prevent contamination between the control and intervention groups, we randomize participants at a cluster level, each cluster representing hospital units with distinct catchment areas.

There is a need for rigorous methods for defining and monitoring quality of implementation of evidence based practices (EBPs) [58]. This is of particular relevance for ACP and other practices where the implementation is low [6, 9, 15, 23, 30, 66, 67]. Fidelity of implementation is mostly not reported in ACP studies. There is also currently an absence of benchmarks or minimum standards for implementing ACP against which a comparison can be made [17].

We have developed the first validated ACP fidelity measure to improve both ACP research and implementation, with subscales that assess the implementation level, penetration rate and the content and quality of the ACP. This trial is thus a contribution to how ACP can be defined and assessed comprehensively as an EBP. It also incorporates a standard on how to implement ACP for all stakeholders. Hence this is also a contribution to a unified approach which is lacking in the field of research [30, 67].

The project has a strong focus on sustainability and feasibility, such as assisting the clinical units to incorporate selected implementation interventions into their routines, procedures and day-to-day practice. We emphasize a whole ward approach, as the focus on education and staff competence is suggested as important for a sustainable ACP intervention that lasts beyond the active implementation phase of a research project [68, 69]. We have already found that the lack of time and misconceptions about ACP are main barriers to ACP at the clinical level. Providing practical training for health professionals, particularly regarding how to start ACP, are important facilitators [53]. At institutional level, standardizing how to document and communicate ACP across levels were reported as the most important facilitators, and will therefore be among the implementation strategies where the project will strive to develop sustainable solutions.

ACP outcomes are influenced by the systems’ complexity, and evaluations need to consider the context. A major strength of this project is that the project design emphasizes strong stakeholder involvement before, during and after the project. The health care personnel, the frail older adults, their next of kin, the services and health administrators, and the policymakers will play an important role in the development of effective implementation strategies and optimizing the implementation and clinical interventions, e.g. as experts by experience in the local training and as stakeholder/co-researchers and informants. Together with the formative evaluation we will use qualitative method alongside the CRCT, as studies involving both CRCTs and qualitative research can give insights that is useful for understanding variation in outcomes, the mechanism by which interventions have an impact, and identifying solutions [70]**.** The value of qualitative research alongside a CRCT and of formative evaluation may contribute to optimizing the intervention and may improve the implementation. Additionally, the data will provide information and can be used to explore the feasibility, acceptability and implementation of the intervention to help understand how it was, or why it was not effective [71].

There is little or no research assessing whether the content from the ACP follows the patient and is used when the patient is transferred to another level of health care. Further, there is more limited research on ACP in primary care. This is a paradox, since family physicians have a central role for all patients in providing, coordinating, referring and planning of health care services, and could have the opportunity to initiate or follow up ACP [72]. A family physician who knows the patient well can play an important role in ensuring the intended consequences of ACP for the frail older adults and their close relatives. It is a limitation of this trial that we implement ACP in hospital wards, without an active focus through the research or implementation strategies on collaboration between health care levels or on follow-up of the conversations in the primary health care. The rationale behind selecting geriatric wards was mainly that Norwegian hospitals and Norwegian general practitioners by large are unfamiliarised with ACP, and we regarded the culture in the geriatric milieu as a natural starting point. Hopefully, further research and implementation will result in ACP at all levels, including the collaboration between levels.

The project outcomes, when interpreted in context, may be valuable across nations with both similar and diverse welfare services and health laws, e.g. to improve the implementation of evidence-based knowledge and ACP for frail older adults. Our approach fills an evidence gap critical to health service planners, and the lesson learnt from this project can enable recommendation for future services. The qualitative study of barriers and facilitators for ACP at the Organizational- and System level and the health economic analysis are contributions to lift the implementation of ACP to a broader societal and public health perspective. Our project may provide valuable knowledge to the fields of ACP, geriatrics, shared decision-making in frail older adults, health service research and implementation science. Furthermore, the project will illuminate critically and informatively the different stakeholder’s needs and difficulties with ACP.

